### Eligibility for study outcomes

The following definitions will be used to determine participant eligibility for study outcomes and analyses (see Fig. 1).

#### Screening failure

Couples who are deemed a *screening failure* will be ineligible for all study outcomes and not form part of the evaluable population for analyses, including the primary modified intention-to-treat (mITT) analysis and per protocol analysis. A *screening failure* occurs if i) a female declines participation to the full trial following screening at a site without an onsite laboratory, ii) a partner declines participation after the female has enrolled, iii) a couple is unable to be contacted for recruitment procedures, iv) the male is ineligible, v) a female has a screening slide subsequently scored as NS = 0–3 when it processed at the Central Co-ordinating site, and vi) female participants requiring or recalled within the first week of enrolment for treatment of PID requiring 14 days of metronidazole +/− ceftriaxone.

#### Protocol violation

The following are defined as protocol violations and are ineligible for the primary mITT analysis and per protocol analysis (as defined below) but may be eligible for other analyses: i) a female who does not return for any clinical assessment, ii) a female who formally withdraws at any point during the study and has either provided no data at all or states previous data cannot be used, iii) a male participant who formally withdraws prior to day 8 (NB. if he withdraws after providing day 8 data on adherence and his partner is happy to continue her data can still be used in all analyses and his data can be used in safety analyses), iv) a male partner does not provide any baseline specimens, questionnaire or signed PICF, v) a female who does not take any antibiotic therapy, or vi) a male partner randomised to the intervention group who does not use any antibiotic therapy.

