**Fig. 1 Fig1:**
[figure not shown]
Participant flow through the study from recruitment to study endpoint. ^1^been together ≥8 weeks, indicated/confirmed on phone that RSP likely to participate; ^2^refer to eligibility criteria; ^3^protocol violation means not in modified intention-to-treat (mITT) primary analysis or per protocol analysis; ^4^eligible for mITT and per protocol analyses if week 4 and/or 12 provided but with missing data, not eligible for safety analysis; ^5^if female participant does not attend clinic visits but does return a swab, eligible for secondary endpoints; ^6^if female attends at week 4 but not week 12, still be eligible for mITT; if no visits but returns a swab, eligible for secondary endpoints; if no visits or swabs, protocol violation. Abbreviations: LTFU, Loss to follow up; W, withdrawn

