#### Recruitment of male partners

After a recruited woman confirms with the research team that her partner is interested in participating in the trial, a time will be made to speak with him (either immediately if he is present in clinic or via a telephone recruitment consultation). The research nurse will first provide a detailed explanation of the trial, check for trial eligibility and any contraindications to medication, with review by a clinician as required prior to randomisation. For all males, once trial and medical eligibility have been documented in an electronic medical record, written informed consent will be obtained. *For a male present in person* this will be written informed consent from the outset. *For a male on the phone*, initial verbal consent will be documented in the electronic medical record, and then written informed consent will be obtained by return of the signed PICF with the baseline recruitment pack. Following consent, randomisation will be performed. If a male is randomised to the *intervention group*, he will be instructed on how to use the medication. All male participants, regardless of randomisation group will be instructed to collect baseline genitourinary samples (urine and penile skin sample) and refrain from any sexual contact for the 7 days that their partner is taking medication (or, while they are taking their medication if randomised to the *Intervention group*). Study material (i.e. specimen collection materials and questionnaires) and medication (if randomised to the *Intervention group)* will be provided in person or will be couriered to the participant’s home.

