### Statistical methods

Analysis and reporting of the trial will be in accordance with the Consolidated Standard of Reporting Trials (CONSORT) guidelines. A detailed Statistical Analysis Plan will be written close to final data lock, but before any analyses are performed, that will define all analyses in detail. Enrolment and longitudinal specimen and questionnaire data will be entered into two separate password-protected online databases within REDCap and then imported into a statistical package (Stata) for analysis.

The Primary Analysis is a mITT analysis. All randomised women will be analysed as randomised if they 1) returned for ≥1 clinical visit, 2) took one or more doses of antimicrobial therapy, and 3) are part of the evaluable population. Sensitivity analyses will include analyses that take into consideration adherence to treatment (for women and/or men). Women who attend at week 4 but not week 12, are still eligible for the primary outcome analysis. Primary analyses will be simple unadjusted two-group comparisons of the randomised arms using Cox regression. If there are important imbalances in baseline characteristics, further adjusted analyses will be performed. Cox regression analyses will be also used to assess co-variates associated with recurrence including demographics, sexual practices, contraception use, smoking and other factors previously shown to be associated with BV recurrence.

Secondary analyses include a per protocol analysis for participants qualifying for the mITT population and who adhered to ≥70% of doses of the medication(s) prescribed (i.e. ≥10 doses of a 14-dose prescription or ≥ 5 doses of a 7-dose prescription). Any AEs leading to cessation of treatment, and all reported clinical AEs will be summarised descriptively. This will include every male who took ≥1 dose of at least one of the investigational drugs.

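### The primary mITT set drops randomised women for what their male partner does after allocation, under one rule that can act only in the intervention arm, and the statistics section defines a different set

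*Protocol article*

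**What the plan says.** Protocol violation opens: "The following are defined as protocol violations and are ineligible for the primary mITT analysis and per protocol analysis". Of its six items, three depend on the man alone:

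- (iii) "a male participant who formally withdraws prior to day 8". A note adds that the woman's data remain usable if he leaves after giving day 8 adherence data and she is content to go on, so earlier withdrawal removes her.
- (iv) "a male partner does not provide any baseline specimens, questionnaire or signed PICF".
- (vi) "a male partner randomised to the intervention group who does not use any antibiotic therapy".

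A footnote to Fig. 1 repeats the consequence: "protocol violation means not in modified intention-to-treat (mITT) primary analysis or per protocol analysis".

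Statistical methods sets out the primary population differently: "All randomised women will be analysed as randomised if they 1) returned for ≥1 clinical visit", took at least one dose, and belong to the evaluable population. Screening failure and Allocation tie the evaluable population to not being a screening failure. Items (iii), (iv) and (vi) do not appear in this definition.

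On timing, a man recruited by phone gives consent in two steps: "initial verbal consent will be documented in the electronic medical record, and then written informed consent will be obtained by return of the signed PICF". Randomisation follows consent, and the study pack and any medication are then handed over or couriered. Allocation states that participants know their group and refers to violations arising after randomisation.

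**The concern.** The primary outcome is measured in the woman. She may have taken her treatment and attended every visit, yet be left out because of her partner's conduct once the couple's arm was known. Rule (vi) cannot apply to a control couple, because control men are given nothing to take. Rules (iii) and (iv) are worded for both arms, but they follow known allocation, and only intervention men face a course of treatment, so their frequency may differ by arm.

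If the removed women differ from the others in recurrence risk, the arms are no longer comparable and the hazard ratio absorbs the difference. The named sensitivity analyses are based on adherence and do not bring these women back. No analysis of all randomised couples is named. With two definitions in print, the choice between them also remains open in a trial where allocation is known to participants and to the nurse who randomises.

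**Working it through.** **Inputs from the article (Sample size).** Recurrence 40% in control and 24% in intervention, two-sided 5%, power 80%, 145 per arm, 15% loss, 342 couples in all (171 per arm).

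**The plan's own figure.** The two-proportion formula without correction is [1.96·√(2·0.32·0.68) + 0.842·√(0.40·0.60 + 0.24·0.76)]² / 0.16² = 132.3, so 133 per arm. The continuity correction gives 145 per arm, or 290 couples. Then 290/0.85 = 341.2, rounded up to 342. The stated sizes reproduce and are not in dispute. At 145 per arm the uncorrected formula gives 83.5% power.

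**The two definitions side by side.**

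| Ground for leaving the mITT | Protocol violation and Fig. 1 | Statistical methods |
|---|---|---|
| Woman attends no clinic visit | yes | yes |
| Woman takes no antibiotic | yes | yes |
| Man withdraws before day 8 (iii) | yes | not listed |
| Man does not return baseline pack or signed form (iv) | yes | not listed |
| Intervention man uses no antibiotic (vi) | yes | not listed |

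**Possible bias from a one-arm exclusion.** Assume no treatment effect, so 40% recur in each arm as randomised. Remove a share x of intervention couples whose women recur at risk q. Neither x nor q is in the article; both are assumed ranges. The observed intervention risk is (0.40 − x·q)/(1 − x). The last column is the chance of a significant result favouring the intervention (nominal 2.5%), from a pooled z-test with 145 controls and 145(1 − x) intervention couples.

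| x | q | Observed risk | Risk ratio | False result for intervention |
|---|---|---|---|---|
| 2% | 70% | 39.4% | 0.985 | 3.2% |
| 5% | 50% | 39.5% | 0.987 | 3.1% |
| 5% | 70% | 38.4% | 0.961 | 4.6% |
| 10% | 50% | 38.9% | 0.972 | 3.8% |
| 10% | 70% | 36.7% | 0.917 | 8.2% |
| 10% | 40% | 40.0% | 1.000 | 2.5% |
| 10% | 25% | 41.7% | 1.042 | 1.25% |

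Example: (0.40 − 0.10·0.70)/0.90 = 0.367, and 0.367/0.40 = 0.917. The planned model is Cox regression. Converting by ln(1 − p)/ln(0.60), the 5-10% removed, 50-70% risk cases give hazard ratios of about 0.98 to 0.89.

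**Cost of keeping the women.** If a share x of intervention couples has an untreated man and recurs at 40%, the as-randomised intervention risk is (1 − x)·0.24 + x·0.40. At x = 2%, 5%, 10% and 15% this is 24.3%, 24.8%, 25.6% and 26.4%. Power at 145 per arm (uncorrected) is 82%, 79%, 75% and 69%, against 83.5% at x = 0.

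**The case against.** Several points on the other side have force.

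- **Direction.** A reader might infer that the exclusions favour the intervention. That requires removed women to recur more often than average, and the article gives no such figure. Its Background reports more recurrence with an ongoing regular partner than with none or a new one. If men who never start or who withdraw early reflect partnerships that are ending, the removed women could recur less often. Exclusions of control couples under (iii) and (iv) could also offset or reverse any imbalance. This objection stands.
- **Size.** Nothing in the article suggests that 10-15% of eligible, consenting men would use no dose at all. This stands; at 2% the effect is negligible.
- **Question asked.** A reader might infer that the trial set out to test an offer of partner treatment, so that the mITT answers another question. Objectives speaks of concurrent treatment and of treated partners, not of an offer, although the Discussion calls the trial pragmatic. The point rests on comparability of the arms, not on that reading.
- **Screening failures.** "a partner declines participation after the female has enrolled" might be read as covering refusals after allocation. Recruitment of male partners puts eligibility checks and consent before randomisation, and the allocation button appears only once the couple is deemed eligible, so the natural reading is before allocation. The text does not say so outright, and a clarifying clause is enough.
- **Consent.** Written consent is an inclusion criterion for men, so (iv) partly enforces eligibility. That justifies leaving out his data. It does not require discarding the outcome of a woman who gave her own written consent.
- **Conflict between sections.** The Statistical methods definition is not purely about the woman: the evaluable-population condition brings in couple-level screening rules. The gap is narrower for that reason, but (iii), (iv) and (vi) are protocol violations, not screening failures, and are still absent there.

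An analysis plan not shown here could settle the matter. The article nonetheless states the exclusions outright, in two places.

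**Conclusion.** The point holds as a defect in the definition of the primary set. Randomised women are excluded for the partner's conduct after allocation. One rule acts in a single arm by construction, two more can act unequally, and the sections disagree on whether any of the three applies. The comparison is not fully protected by randomisation and can be biased.

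How much, and which way, cannot be read from the article. With no true effect and 5-10% of intervention couples removed at 50-70% risk, the risk ratio would be about 0.99 to 0.92, and the chance of a false result for the intervention 3.1% to 8.2% instead of 2.5%. Those figures rest entirely on the assumed x and q and model only one-arm removal. A firm claim of bias towards benefit is not supported.

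**What to change.** Reconcile Protocol violation, the Fig. 1 footnotes and Statistical methods into one primary set that follows Statistical methods: couples randomised and not screening failures, with at least one clinic assessment and at least one dose taken by the woman, analysed as randomised whatever the man did after allocation. Apply (iii), (iv) and (vi) only to the per-protocol set. Where the man's signed form is missing, omit his data and keep the woman's outcome under her own consent. Report the present mITT as a sensitivity analysis. State that screening failure on partner grounds applies only before allocation.

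The work is mainly wording, plus the use of outcomes collected anyway. The real cost is dilution. With 10% of intervention couples retained at 40% recurrence, the target contrast becomes 40% against 25.6% and power at 145 per arm is about 75% instead of 83.5% (uncorrected formula). At 2% retained it is 82%. The revised set still depends on the woman's attendance and dosing after randomisation, but those conditions are the same in both arms and already part of the plan.

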#### Protocol deviation

The following are considered protocol deviations i) if a male participant does not return their day 8 questionnaire, they are not eligible for the safety analysis which measures AEs, or ii) if a female participant does not attend any clinic visits for clinical assessment but returns ≥1 swab, she is eligible for the Nugent and microbiota secondary endpoints only.

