#### Home and clinic follow up

Female participants will collect samples and complete questionnaires on four occasions after baseline including the day after completing antibiotics (day 8), and at weeks 4, 8 and 12 (Table 1, Fig. 2). At scheduled clinic visits (weeks 4 and 12) females will be assessed for BV by Amsel and Nugent criteria, and will complete a questionnaire. At day 8 and week 8, swabs, slides for Nugent scoring, and questionnaires completed at home will be returned by replied paid post to MSHC. If a woman returns a home slide with NS = 7–10, or reports symptoms indicating BV, she will be booked for an interim clinic visit and assessed for BV. All slides collected at home or in non-MSHC clinics will be sent via post to MSHC for scoring within a week. Slides with morphotypes unable to be easily scored will be read by a second independent microscopist and consensus reached.

Male participants will self-sample and complete questionnaires at enrolment and, for those in the *Intervention group*, the day after completing treatment (day 8), or if in the *Control group*, the day after their partner has finished her treatment (Fig. 2). Men will be instructed to complete their follow up specimens and questionnaires at the same time as their partner. All male questionnaires and specimens will be collected at home and returned by replied paid post to MSHC.

Validated questionnaires at each time point will collect data detailing sexual practices (e.g. frequency and types of sex, condom use, change in partnerships), contraceptive use, menstrual dates, genital symptoms, and any interim treatments. Adherence and AEs will be recorded on day 8 questionnaires and participants instructed to call the dedicated study phone if they have any enquiries or are concerned about any AEs experienced.

A reminder SMS will precede each scheduled self-collection time point and reminders sent for up to 2 weeks if samples are not returned, after which a participant will be classified as a non-responder for that interval, but contacted at the next follow-up point. A reminder SMS will be sent to participants 1–2 business days prior to any clinic-based appointment. All couples will receive a $10AUD voucher for each completed stage of follow-up.

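### Two definitions of the male safety set conflict: one requires a returned day-8 questionnaire, the other at least one dose, so men who stop early because of an adverse effect may be missed

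*Protocol article*

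**What the plan says.** Four places in the protocol article bear on who is in the safety analysis of men.

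- **Protocol deviation**, item (i), makes return of a form the condition: "if a male participant does not return their day 8 questionnaire, they are not eligible for the safety analysis which measures AEs".
- **Statistical methods** makes exposure the condition. It first sets the content, "Any AEs leading to cessation of treatment, and all reported clinical AEs will be summarised descriptively", and then the population: "This will include every male who took ≥1 dose of at least one of the investigational drugs".
- **Fig. 1, footnote 4**, appears to side with the form-return rule: "eligible for mITT and per protocol analyses if week 4 and/or 12 provided but with missing data, not eligible for safety analysis".
- **Protocol violation**, item (iii), concerns men who withdraw formally. It allows a man's data into the safety analyses "if he withdraws after providing day 8 data on adherence", and does not say what happens to safety data from a man who withdraws sooner.

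Adverse events can arrive by more than one route. Home and clinic follow up names the main one, "Adherence and AEs will be recorded on day 8 questionnaires", and then a second: "participants instructed to call the dedicated study phone if they have any enquiries or are concerned about any AEs experienced". Under Data safety and monitoring, the Trial Management Committee also assesses adverse events and compiles them for the Data Safety Monitoring Board.

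**The concern.** The two rules define one analysis in different ways. They differ for a man whose dosing, or whose adverse event, is known although he sent no day-8 form. An analyst cannot follow both.

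The choice matters because return of the form comes after treatment begins and may depend on how treatment was tolerated. A man who gives up in the first week because of an adverse effect, or who withdraws from the trial, may be less likely than others to return it. Selecting on return could then lower both the overall adverse-event rate and the rate of stopping because of an adverse event, which Statistical methods singles out for reporting.

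Adverse effects in men are a named additional outcome. The men are treated outside approved indications, and the Discussion foresees changes to treatment guidelines. An understated rate would favour adoption of partner treatment.

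**Working it through.** **The two rules side by side**

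| Intervention-arm man | Form-return rule (Protocol deviation) | One-dose rule (Statistical methods) |
|---|---|---|
| Took at least one dose, returned the form | In | In |
| Stopped early, stayed in the trial, returned the form | In | In |
| Known to have taken a dose, no form | Out | In |
| Telephoned about an adverse event after dosing, no form | Out | In |
| No form, use unknown | Out | Cannot be shown to qualify |

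The contradiction lies in the third and fourth rows. The second row rests on the control-group section, which lets participants stop treatment and remain in the trial.

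**How large could the effect be?** The plan states no figure to reproduce here. The only relevant number is the arm size: 145 / 0.85 = 170.6, rounded up to 171 couples per arm, as Sample size states. The article gives neither the proportion of men without a day-8 form nor the proportion stopping because of an adverse event, so everything below is assumed.

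Non-return of 5%, 15% or 25% among 171 treated men removes 8.55, 25.65 or 42.75, that is about 9, 26 or 43 men.

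Let *a* be the true proportion stopping because of an adverse event, *m* = 0.15 the overall non-return proportion, and *r* the risk of non-return in stoppers relative to other men.

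- Non-return in other men: b = m / (1 − a + a·r)
- Non-return in stoppers: s = r·b
- Rate reported under the form-return rule: a·(1 − s) / (1 − m)

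For a = 0.10:

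- r = 1: s = 0.15; reported 0.10 × 0.85 / 0.85 = 10.0%; about 3 stoppers lost (171 × 0.10 × 0.15 = 2.6)
- r = 2: b = 0.15 / 1.1 = 0.136, s = 0.273; reported 0.10 × 0.727 / 0.85 = 8.6%; about 5 lost
- r = 4: b = 0.15 / 1.3 = 0.115, s = 0.462; reported 0.10 × 0.538 / 0.85 = 6.3%; about 8 lost

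| True stopping rate | r = 1 | r = 2 | r = 4 |
|---|---|---|---|
| 5% | 5.0% | 4.2% | 2.8% |
| 10% | 10.0% | 8.6% | 6.3% |
| 20% | 20.0% | 17.6% | 14.7% |

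The direction also depends on *r*. If men without symptoms are the poorer responders, say r = 0.5 with a = 0.10, then b = 0.15 / 0.95 = 0.158, s = 0.079, and the reported rate is 0.10 × 0.921 / 0.85 = 10.8%, slightly too high.

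**The case against.** The best defence is that the two statements do different jobs: Statistical methods sets exposure and Protocol deviation sets who can be evaluated. The day-8 form records both adherence and adverse events, so for most non-returners the missing form is also the missing evidence of a dose. This stands in part. It confines the conflict to men whose dosing or adverse event is known another way, but it does not remove it, because the study phone is such a way and Statistical methods promises to cover all reported events.

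Several stronger readings are tempting, and the article does not support them.

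- *Men who stop because of an adverse effect are lost.* Only those who also return no form would be. Reminders run for up to two weeks and each completed stage earns a voucher.
- *Early withdrawers are barred from the safety analysis.* Protocol violation does not say so. Its note is permissive, and its opening allows that violators may enter other analyses.
- *The Fig. 1 footnote settles the matter.* Its words, "but with missing data, not eligible for safety analysis", name neither men nor the day-8 form, and the figure is not shown.
- *Telephoned adverse events are discarded.* No passage says this. The committee route carries no questionnaire condition. At most, such an event falls outside the tabulated safety analysis.

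It is also fair to say that male adverse effects are an additional outcome, summarised descriptively without a test.

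**Conclusion.** The point holds as a contradiction between Protocol deviation (i) and Statistical methods over the male safety set, with a possible downward bias if the form-return rule is the one applied. The contradiction follows from the text alone. The bias does not: it needs non-return to be more common among men with adverse effects, and the article has no data on that. With 15% non-return and up to a fourfold relative risk, the assumed cases run from no distortion (10.0% reported as 10.0%) to a 10% rate reported as 6.3%. These figures show sensitivity and do not estimate what will happen.

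A reader might infer that the safety results are bound to be understated. The article does not support that. Severity is moderate: the reported safety denominator is ambiguous until the sections are reconciled, but the primary efficacy analysis and the sample size are untouched.

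**What to change.** 1. Delete the safety exclusion in Protocol deviation (i), and align Fig. 1 footnote 4 and Protocol violation (iii) with it.
2. Use the Statistical methods definition throughout: every man known to have taken at least one dose of at least one study drug.
3. Count adverse events from every source already in the plan: the day-8 questionnaire, the study phone and the events compiled by the Trial Management Committee. Include men who withdraw, unless they refuse use of their data.
4. Print the number of intervention-arm men without a day-8 form beside each rate, and base questionnaire-derived rates on men with data.
5. Add a sensitivity bound for stopping because of an adverse event that treats men with missing forms as events. With a = 0.10 and 15% non-return, it is a·(1 − s) + 0.15: 23.5% for r = 1 (0.085 + 0.15) and 20.4% for r = 4 (0.054 + 0.15). It is wide, and should be labelled a bound.

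Men whose use is unknown should not be added to the main denominator. That departs from the one-dose definition and, with no further reports, dilutes the rate to a·(1 − s): 8.5% for r = 1 and 5.4% for r = 4, below the 10.0% and 6.3% that the form-return rule would give.

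The cost is wording in the protocol and analysis plan before data lock, and one added sensitivity analysis. No new data collection is needed.
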